#### Data management {19}

Data will be managed by an external data monitoring center. The secure database will be managed according to the standard operating procedures and will remain in secure locations on site throughout the entirety of the study.

#### Confidentiality {27}

In order to maintain patient privacy, data capture tools, study drug accountability records, study reports, and communications will identify the assigned patient number. Confidentiality standards are maintained by coding each patient enrolled in the study through the assignment of a unique patient identification number. Patient names or any identifying information will not be included in the aggregate data that are transmitted for analysis. Only site enrollment logs maintained by research coordinators in charge of data acquisition will contain any personal identifiers. These logs will remain in a secure location on site for the duration of the study. Only research coordinators will access this information. Additionally, the site investigators will grant monitor(s) and or its designee access to the patient’s original medical records, including medical history, laboratory studies, and medication administrations, for verification of data gathered and auditing the data collection process. This information will be accessed for the duration of the study for the purpose of data verification and reconciliation.

#### Plans for collection, laboratory evaluation, and storage of biological specimens for genetic or molecular analysis in this trial/future use {33}

A sample of convenience (*n* = 15) of all catheters removed for suspected or confirmed CLABSI or colonization during work hours at the lead investigators site will be collected and used for the analysis of biofilm formation and classification of microorganisms. The same number of CVADs removed from patients who no longer require a CVAD with the absence of colonization will also be collected to act as a control comparator in this analysis. Upon removal, these CVCs will be placed in specimen bags stored at 4 °C. These catheters will then be processed by study personnel before shipment to [name] lab at the Vaccine and Infectious Disease Organization-International Vaccine Centre (VIDO-InterVac) for further analysis. These will include culture-dependent and culture-independent classification of microorganism colonies and analysis of biofilm, according to internal standard operating procedures.

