## Objectives {7}

### Primary objectives

The primary objective is to compare the incidence rate of CLABSI, catheter occlusions requiring replacement, and alteplase use present in critical care patients with CVADs locked with 4% tetrasodium EDTA versus critical care patients with CVADs locked with the standard of care of saline or citrate.

For the purpose of this study, these outcomes will be evaluated using a composite outcome consisting of the incidence rate of catheter obstruction requiring alteplase, CLABSI (diagnosed in accordance with NHSN definitions [29]), or CVAD replacement due to occlusion. As current surveillance guidelines do not include routine CVAD occlusion reporting, the use of alteplase specifically for the treatment of CVAD occlusion has been identified as a proxy method to track the occlusion rates.

The secondary objectives include the incidence rate of each component of the composite outcome separately, and other outcomes that may be modifiable with change to catheter locking practices, including: the incidence of catheter colonization (as identified by the standard clinical and microbiology operating procedures at each institution enrolled in the study), incidence of catheter-associated venous thrombosis, direct cost related to alteplase use for catheter occlusion, other costs related to treatment and diagnosis of relevant CVAD complications, and classification of microbial species isolated from colonized catheters.

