### Trial design {8}

The trial is a multi-center, cluster-randomized, double-blinded, crossover trial. Five ICUs/high acuity units (HAUs) across Canada will participate. The ICU/HAUs will be assigned at random to administer either the 4% EDTA locking solution (intervention) or the standard of care saline or citrate (control) during the first four-and-a-half-month period. ICU/HAUs will then cross over and administer the other locking solution during the second 4.5-month period. Patient recruitment will cease at the end of three-and-a-half months during each period to ensure all patients can be followed for 28 days. The study protocol will commence at each site via a staggered start (see Fig. 1).

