#### Secondary outcomes

All outcomes will be assessed twice daily via reviewing the patient charts and participating in discussions with the patients’ treating nursing staff. The outcomes will be tested for and diagnosed according to clinicians in charge of patient care.Incidence rate of confirmed CLABSI (as adjudicated according to the NHSN criteria described previously).Incidence rate of suspected CLABSI. A case of suspected CLABSI will be defined as a case in which no microbiological testing was performed on the suspected catheter or through-catheter blood sample, with the patient having a positive blood culture result of a common bacteria associated with a CVAD infection with no other identifiable source of infection.Incidence rate of catheters requiring removal due to occlusion, as determined by inspecting relevant notes on the patient chart and discussion with the nursing staff.Incidence rate of catheters requiring alteplase use as determined by inspecting relevant notes on the patient chart and discussion with the nursing staff.Incidence rate of catheter-associated venous thrombosis, as determined by inspecting relevant medical imaging and notes on patient charts.Incidence rate of catheter colonization, as diagnosed according to the Clinical Practice guidelines of Infectious Diseases Society of America [31].Classification of types of microorganisms isolated from a convenience sample of removed CVAD’s through culture-dependent and independent techniques.Health economic evaluation of the cost of intervention versus health care utilization and associated costs of diagnosis and treatment of catheter complications

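### The 15 + 15 catheters for the microbiology outcome have no allocation by period, so the one-site sample can be lopsided by lock and its controls can come from the other lock

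*Protocol article*

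**What the plan says.** - **Status of the outcome.** Under Primary objectives, classification of microbial species stands in the list introduced as "other outcomes that may be modifiable with change to catheter locking practices". Under Secondary outcomes it reads "Classification of types of microorganisms isolated from a convenience sample of removed CVAD’s through culture-dependent and independent techniques".
- **Cases.** Section {33} specifies a convenience sample of 15: "of all catheters removed for suspected or confirmed CLABSI or colonization during work hours at the lead investigators site will be collected".
- **Controls.** The same number of catheters, removed because they were no longer needed and "with the absence of colonization will also be collected to act as a control comparator in this analysis".
- **Design.** Each site uses one lock in the first period, and then "ICU/HAUs will then cross over and administer the other locking solution during the second 4.5-month period". Section {20c} says that only one of the two locks is on hand at a site in a given period, and the Discussion confirms a single crossover.

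Section {33} sets no number per period or per lock for cases or controls.

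**The concern.** At the lead site, calendar time decides the lock. A sample drawn by convenience, with no rule about when, may contain few catheters from one of the two locks. Three things are at stake.

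1. **Between-lock description.** The objectives place species classification among outcomes that the lock might change. If one lock supplies only a few catheters, little can be said about that.
2. **Case-control comparison.** This is the contrast that section {33} itself names. If cases come mainly from one period and controls from the other, a difference in biofilm or organisms could reflect the lock or the calendar instead of colonization.
3. **No later repair.** The site crosses over once. Catheters not kept in a period cannot be recovered by analysis.

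Selection adds to this. Cases are chosen on an event that EDTA is meant to prevent, so an effective lock would itself thin out the EDTA catheters.

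**Working it through.** The figure of 15 comes with no derivation, so there is nothing to reproduce. The check asks how lopsided the 15 cases could be under two readings of the collection rule.

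**Inputs from the article**
- 15 cases, one site, two periods of 4.5 months, with enrollment in the first 3.5 months of each (Trial design {8}, section {33}).
- 75 of 90 patients eligible in one month at the observed site, and at least 175 recruits per site per period (Recruitment {15}).
- Pooled ICU CLABSI rate of 4.59 per 1000 catheter days; earlier EDTA results of 1.9 to 0.6 per 1000 (Background).
- Planning effect: 30% relative reduction in the composite (Sample size {14}).

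**Assumptions, not in the article**
- The rate r of eligible work-hours removals per month.
- The order of collection.
- 5 to 10 catheter days per patient.
- Equal exposure in the two periods.

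**Reading A: taken in order of removal, stopping at 15.** Let N1 and N2 be independent Poisson counts with mean m = 4.5r, with no lock effect. The first lock gives min(N1, 15). The second gives min(N2, 15 − first-lock count).

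| Rate | m per period | Expected split | P(none from second lock) | P(15 not reached) |
|---|---|---|---|---|
| r = 1 | 4.5 | 4.5 vs 4.5 | 1% | 96% |
| r = 1.5 | 6.75 | 6.8 vs 5.9 | 0.5% | 62% |
| r = 2 | 9 | 9.0 vs 5.5 | 4% | 21% |
| 4% of 75 × 3.5 | 10.5 | 10.4 vs 4.5 | 11% | 7% |
| r = 3 | 13.5 | 12.6 vs 2.3 | 38% | 0.5% |

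Plausible values of r:
- CLABSI alone gives 175 × 5 × 4.59/1000 = 4.0 to 175 × 10 × 4.59/1000 = 8.0 per period, or about 0.9 to 1.8 per month. Suspected and colonized catheters add to this and the work-hours limit subtracts. Neither amount is given.
- r = 3 equals 4% of 75 patients per month carried over all 4.5 months. Enrollment lasts 3.5 months, so 4% of enrolled patients is 75 × 3.5 × 0.04 = 10.5 per period, not 13.5. The 4% is itself an assumption.

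**Reading B: 15 spread evenly over both periods.** If RR is the ratio of eligible removals under EDTA to control, the EDTA share is p = RR/(1 + RR) and the EDTA count is Binomial(15, p).

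| Effect | p | Expected EDTA catheters | P(12 or more from one lock) |
|---|---|---|---|
| None | 0.50 | 7.5 | 3.5% |
| 30% reduction (RR 0.7) | 0.412 | 6.2 | 7.9% |
| 1.9 to 0.6 (RR 0.316) | 0.24 | 3.6 | 50% |

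**What an even split buys.** At 8 vs 7, exact Fisher power for a species share of 60% vs 20% is 27%. At 12 vs 3 it is 12%. At 14 vs 1 the smallest attainable p is 0.067. Even a balanced sample supports description only.

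**The case against.** **The between-lock contrast is not the stated comparison.** Section {33} names colonized against uncolonized catheters, and the outcome is worded descriptively. This stands. The lock contrast is inferred from the lead-in to the list of objectives and from the general sentence on analyzing secondary outcomes. A reader might infer that a planned lock comparison is lost, and the text does not go that far. It does leave the objectives and section {33} pulling in different directions. Moreover, the comparison that section {33} does name is exposed, because its controls have no period rule.

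**Filling in order is not stated.** This also stands. A reader might infer that the sample will come mostly or wholly from the first lock. That needs both a stop-at-15 rule and a high removal rate. At 1 to 1.5 removals per month the split is close to even, and the likelier problem is a sample short of 15. With even sampling, marked imbalance is uncommon unless EDTA works about as well as in the earlier studies, which were in other populations.

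**Details may sit elsewhere.** The full protocol or laboratory procedures may schedule collection, and the article is a condensed text. That is possible. But the article does fix the number, the single site and the convenience rule, and these create the exposure.

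**A quota gains little power.** True, and lock would still coincide with period at one site. The gain is that both locks are represented and that cases and controls share a lock.

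**Conclusion.** The concern holds in a limited form. As written, the sample can be lopsided by lock, and controls can come from a different lock than the cases. The second problem would confound the article's own comparison.

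The size is uncertain. Under in-order collection, the chance of no second-lock cases runs from about 1% through 11% to 38% over the rates considered. Under even sampling, the chance of 12 or more from one lock is 3.5%, 7.9% or 50%, depending on the effect. These figures rest on an assumed removal rate, an assumed collection order, Poisson or binomial counts and equal exposure per period.

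The article does not support saying that the imbalance is expected. The matter touches one secondary laboratory outcome; the primary outcome, its power and the safety data are unaffected. It is still worth correcting, because the change is nearly free and the loss cannot be made good afterwards.

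**What to change.** In section {33}:

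1. Split the same total by period: about 7 to 8 infected or colonized catheters in each, with collection closed separately for each period.
2. Take each control catheter from the same period, and hence the same lock, as its case.
3. Record dwell days and catheter type for every catheter collected. The Background names longer insertion as a risk factor for infection, so imbalance should at least be visible.
4. State that any between-lock result is descriptive, because lock and period coincide at one site, and align the wording of the objectives with this.

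**Cost.** Some wording and a collection log, with no more catheters than now planned. The downside is that a period's quota may not fill, particularly under an effective lock; the number reached should then be reported as it stands. Matching controls on dwell time and catheter type, or adding a second site, would be optional and is not needed to meet this point.

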## Statistical methods

### Statistical methods for primary and secondary outcomes {20a}

Data will be analyzed following the intent-to-treat principle. The primary outcome will be analyzed using a zero-inflated negative binomial (ZINB) model that accounts for clustering within ICU [33]. The ZINB model takes into account: (1) the large percentage (~ 80% expected) who will not have any event and (2) the large variability in the number of events among participants who experience at least one event (individuals who experience one event are more likely to experience additional events). The (log-)time-at-risk will be entered into the model as an offset term. The average treatment effect will be obtained by regression standardization of the composite incidence rates predicted by the ZINB model [34]. Standard errors will be obtained using bootstrapping.

The model will adjust for the study period (first or second) and may adjust for the following individual-level baseline characteristics: age; sex at birth; BMI; APACHE IV score; length of pre-ICU hospital stay (days); presence of multiple CVADs per patient; any suppression of the immune system, defined as post-organ transplantation, acquired immunodeficiency syndrome [AIDS], neutropenia [< 1000 absolute neutrophils], corticosteroids [> 20 mg/day of prednisone or equivalent for more than 6 months], or currently taking immunosuppressive agents (i.e., Imuran, etc.) at time of enrollment into study; site of CVAD insertion (femoral, jugular, subclavian, right or left side); type of catheter used; any catheter additives, as they may confound the result (such as antibiotic impregnation); having a pre-existing central line upon admission to the ICU; and this line had already received a lock, concurrent systemic antibiotic use unrelated to central line infection, concurrent systemic anti-fungal agent use unrelated to central line infection, concurrent systemic administration of anti-coagulants unrelated to catheter occlusion, type of hemodialysis (if applicable), and previously experienced CLABSI or CVAD occlusion.

The secondary outcomes will be analyzed similarly to the primary analysis using generalized mixed effects models (to account for clustering within the unit) appropriate to the type of outcome. Further analysis of the results will include the calculation of costs attributed to healthcare utilization costs between the groups. A complete statistical analysis plan will be developed prior to unblinding and analysis of the data.

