Participants will be enrolled during the first three-and-a-half months of each four-and-a-half--month period. Each participant will be followed until they leave the ICU/HAU, they reach the end of the 28-day follow-up period, or they die. Data collection for incidence rates of confirmed/suspected CLABSI, catheter occlusion requiring removal, catheter obstruction requiring alteplase use, direct cost related to alteplase use for catheter occlusion, and catheter colonization will continue via the combination of in-person discussion and chart review for the duration of time that the patient has their catheter in place, until they are discharged from the ICU/HAU, or they die, whichever comes first. In the event that a blood culture is taken on either the last day of catheter placement or the last day that the patient is in the unit, the research coordinator will continue to monitor the patient charts for the result of that blood culture, as a bloodstream infection may still be attributed to the catheter.

Data collection in the form of monitoring medical imaging results for the incidence rate of catheter-associated venous thrombosis will continue for the entirety of the patients’ ICU/HAU stay, even if all CVADs have been removed. The senior investigators’ clinical experience indicates that thrombosis from a CVAD in the upper thoracic region is sometimes not discovered until weeks after the CVAD has been removed, as it may take this long for the patient to develop symptoms of thrombosis. As such, the research coordinators will continue to follow the medical imaging results of the patients who are still in the ICU/HAU but have had all central lines removed and are no longer receiving the study intervention.

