### Methods for additional analyses (e.g., subgroup analyses) {20b}

Subgroup analysis will be conducted for each participating ICU to assess the potential heterogeneity of treatment effects across sites using a generalized linear model stratified by ICU. Additionally, due to standard of care locking differing between CVCs, IVADs, and PICCs (locked with saline) as compared to hemodialysis catheters (locked with citrate), the authors will perform an analysis of the hemodialysis population both together and separately from the rest of the patient population.

During the COVID-19 pandemic, the expansion and shuffling of ICU and HAU patients to different units of the hospital pose a logistical problem in running experimental protocol (as this would involve having to provide education and oversight of nursing staff beyond the ICU/HAUs). As such, patients who are still designated as ICU/HAU care level, but physically located in another unit, will not receive the locking intervention and will be followed by Research Coordinators for their location in the study. Should they be repatriated back to the physical spaces of the ICU/HAU, they will resume receiving the study locking protocol. Because these patients would have experienced an interruption to the experimental protocol, they will also be analyzed in a separate subgroup.

Finally, recent studies have also provided evidence of a higher risk of catheter occlusion and catheter-associated venous thrombosis among COVID-19 patients, due to the hyper-inflammation and hyper-coagulation associated with the virus [35–37]. As such, we will be collecting data about the COVID-19 status of each enrolled patient. This subgroup will also be analyzed separately, to determine if there are any differences among the COVID-19 population.

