## Trial status

The finalized protocol version is 2.5, May 2022. Recruitment at the lead site began in March 2022. The approximate date when recruitment will be completed at all sites is August 2023.

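### With staggered site starts, a first/second period term does not fully absorb calendar swings, and COVID-19 status, which the protocol links to occlusion, is not among the named covariates

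*Protocol article*

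**What the plan says.** Design (Trial design {8}): "Five ICUs/high acuity units (HAUs) across Canada will participate". Each is randomised to a starting solution, and "ICU/HAUs will then cross over and administer the other locking solution during the second 4.5-month period". Starting dates differ: "The study protocol will commence at each site via a staggered start". Enrolment occupies the first 3.5 months of each 4.5-month period (Participant timeline {13}).

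Calendar span (Trial status): the lead site began recruiting in March 2022, and "The approximate date when recruitment will be completed at all sites is August 2023".

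Primary model (Statistical methods {20a}): a zero-inflated negative binomial model with clustering by ICU and bootstrap standard errors. On time it says "The model will adjust for the study period (first or second"). A long list of optional baseline covariates follows. COVID-19 status is not on it, and no calendar term is named.

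COVID-19 (Methods for additional analyses {20b}): the protocol cites a higher risk of occlusion and catheter-associated thrombosis in COVID-19 patients and says "we will be collecting data about the COVID-19 status of each enrolled patient". The stated use is a separate subgroup analysis.

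**The concern.** In a cluster crossover with one switch, each site contributes one contrast between its second and first period. If all sites start together, a shared calendar swing shifts every contrast equally and the period term removes it. If starts are staggered, the swing shifts the contrasts by different amounts. A shared linear trend still cancels, but a wave or a season does not. What is left depends on which sites were allocated to which order, and five sites, split 3:2 at best, give little averaging.

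COVID-19 is the one source of such a swing that the protocol itself names. It is tied there to occlusion, which underlies two of the three primary components (replacement for occlusion and alteplase use). At stake is how far the single estimate may sit from the truth for reasons that the reported interval may not show.

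**Working it through.** **Plan's own figure.** Inputs from Sample size {14}: risks 20% and 14%, N = 1690, cluster-period SD 0.001, t-test with 10 − 2 − 1 = 7 df. Two-sided alpha 0.05 is assumed. For a 3:2 order split,

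Var = {[0.20×0.80 + 0.14×0.86]/845 + 2×0.001²/5} × 25/24, so SE = 0.0186.

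This gives 78.9% power, in line with the 80% implied by the stated simulation error, since √(0.8×0.2/10,000) = 0.4%. On the log scale, SE ≈ √[(0.80/0.20 + 0.86/0.14)/845/0.96] = √[(4 + 6.14)/845/0.96] = 0.112. This is a risk-ratio approximation to the planned rate model.

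**Possible stagger.** One site recruits over 4.5 + 3.5 = 8 months. March 2022 to August 2023 is at most 18 months, so starts could spread over up to 18 − 8 = 10 months. The text gives no start dates. Fig. 1 was not available for this check, and the end date is approximate, so shorter spreads are also shown.

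**Effect of a shared annual swing.** Let the log rate carry A·sin(ωt + φ), with ω = 2π/12 per month. For a site starting at s, the second-minus-first difference over adjacent 4.5-month windows is

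D(s) = A × [sin(1.178)/1.178] × 2·sin(1.178) × cos(ω(s + 4.5) + φ) = 1.449·A·cos(ω(s + 4.5) + φ).

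For ±20%, A = ln 1.2 = 0.182 and the multiplier of the cosine is 0.264. The period-adjusted treatment contrast is shifted by half the difference between the mean D of the two order groups. Five evenly spaced starts, 48 phases and all 20 allocations (3:2 or 2:3) give:

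| Start spread (months) | Swing | Mean shift | SD of shift | Largest shift |
|---|---|---|---|---|
| 0 | ±20% | 0 | 0 | 0 |
| 2 | ±20% | 0 | 0.034 | 0.083 |
| 3 | ±20% | 0 | 0.050 | 0.120 |
| 9.5 | ±20% | 0 | 0.095 | 0.18 |
| 9.5 | ±10% | 0 | 0.050 | 0.094 |

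Using the 3.5-month enrolment window instead of the whole period raises 0.095 to 0.105. Combined with the design SE, the total is √(0.112² + 0.095²) = 0.147 in the widest case and √(0.112² + 0.050²) = 0.123 at an SD of 0.050.

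**Does the standard error see it?** A simplified simulation used a linear risk-difference model with site and period terms, model-based SE and 7 df. Under no treatment effect, with a 20% wave and a 10-month spread, the empirical SD was 0.028 against a model SE of 0.020, and type I error was 9 to 10%. At a 3-month spread it was 3 to 4%. With no wave it was about 2%.

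**Cost of a calendar term.** In the same simulation at a 10-month spread, adding calendar quarters or annual harmonics brought type I error to 1 to 2%. It raised the SE from 0.0198 to 0.0242–0.0248, a variance ratio of about 1.5 to 1.6. Power at a risk ratio of 0.70 fell from about 80% to 61–64%; at a 3-month spread it was about 77%. A 3 to 4 df spline at 9.5 months inflates the variance by about 1.4 to 1.8 on average over allocations.

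**The case against.** A reader might infer that the treatment effect will be biased. The documents do not support that. Order is randomised, and the shift averages zero over allocations in every row of the table. A reader might also take a true rate ratio of 0.70 to be liable to land anywhere from 0.70·e^(−0.18) = 0.59 to 0.70·e^(0.18) = 0.84. Those are the extremes over all phases and allocations at the widest assumed stagger. In 72% of those combinations the shift is below one design SE, and at ±10% it always is.

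The size also rests on inputs that are not in the text: neither the start dates nor any seasonal amplitude for the outcome is given. With a short stagger and a modest wave the effect is small.

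The simulated error rates cannot be ascribed to the planned analysis. The bootstrap scheme and the cited clustering method are not detailed, and a cluster-period effect may be part of them. The sample-size model does include one, although its assumed SD of 0.001 allows for almost no site-specific change.

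Finally, the covariate list is optional and a full analysis plan is promised before unblinding, so COVID-19 status is not ruled out. Patient-level status would in any case miss season and unit strain.

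All of this stands, and it limits the point. It does not remove it: the protocol does fix the time adjustment as a two-level period term, and that term does not match staggered starts.

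**Conclusion.** The point holds as a moderate one. Under staggered starts the first/second term leaves part of any non-linear calendar swing in the treatment contrast. This is chance confounding in one realised allocation of five sites, and it may be missing from the standard error. On the assumptions of evenly spaced starts and an annual cycle shared by all sites, its SD on the log rate ratio runs from about 0.03 (±20%, 2 months) to 0.095 (±20%, 9.5 months), against about 0.11 for sampling error. So it ranges from minor to nearly as large as the sampling error, and the text cannot settle which. The clearest gap is COVID-19 status: the protocol calls it a risk factor for occlusion and collects it for each patient, but does not list it for adjustment.

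**What to change.** 1. Keep the first/second term in the primary model.
2. Add COVID-19 status at enrolment as a pre-specified covariate in the primary model. Status is already to be collected, so no new data and negligible precision are at stake. The protocol does not say when status is recorded. The analysis plan should therefore state that the value at enrolment is used, so that the model does not condition on infection acquired later.
3. Pre-specify, before unblinding, a sensitivity analysis that adds a parsimonious calendar-time term shared across sites, and report it beside the primary result. The cost is analysis-plan wording and a few parameters.

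The calendar term should not become primary by default. With five sites and one switch each it is partly collinear with treatment, and under a wide stagger the loss of power shown above is substantial. If the actual start dates prove close together, both the problem and the cost of the term shrink.
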